### Primary Outcome Measure

As change in over-ground CWS is an important, valid, sensitive, and reliable measure of poststroke recovery and walking function [56], we chose difference in CWS between groups, from pre- to posttraining as our primary outcome measure [57,58]. On the basis of our power analysis, we planned to include baseline-walking speed as a covariate, if it was significantly related to CWS at pre- and posttraining.

### Secondary Outcome Measure

We plan to report descriptive data on the following secondary exploratory outcome measures: FWS, 6MWT, BBS, GDS, SIS, and ABC scores, with mean and SDs. However, we will not include these variables in our main analysis, as we are not appropriately powered to include them.

### Subgroup Analysis

In addition to these main assessment measures, we also recorded BWS levels, HR, and RPE exertion changes, total number of steps, and distance covered during each session, for participants in both training groups. Descriptive data analysis along with subgroups comparative analysis will be performed on these variables, from pre- to postintervention and on a week-by-week basis, and will be reported in another manuscript. We will also assess feasibility and compliance of each group to either intervention, along with ability to maintain target HR intensity during training. These subgroup analyses will help in better understanding the impact of training on functional walking outcomes and impact on community ambulatory function.

### Survey Data Analysis

Participants in both groups also completed our custom-designed study survey at the end of each training week. The survey consisted of questions on the 9 essential challenging mobility skills that we identified using the research criteria specified by Patla et al [25]. The survey questionnaire consisted of the following 3 subparts: (1) identify which of the 9 essential challenging mobility skills you have difficulty with in your daily life (using yes/no responses); (2) rank in order of importance (1-9), which of the 9 essential mobility skills is most important for you in improving walking function; and (3) respond to specific questions on your training experiences (using a Likert scale 1-7; see Multimedia Appendix 2). We will assess survey data responses for change in responses, ranking of task difficulty, and change in Likert scale scores, respectively.

### Criteria for Data Analysis

We will only be considering those participants in our final analysis, as a data point, if they completed their first week of training. Participants will not be included in our final analysis if they were unable to complete the first week of training, for reasons such as personal time limitations, conflicting time commitments, family crises, and personal psychological factors such as depression and medical procedures.

## Results

### Total Participants Enrolled in Our Study

We assessed 77 individuals with chronic mild to moderate hemiparesis, and excluded 38 individuals who did not meet our inclusion criteria, from June 2012 to January 2015. We enrolled and randomized a total of 39 individuals post stroke for our study, with 19 participants in the HF group and 20 participants in the HF+C group. Data collection along with 6-month follow-up continued until January 2016. Detailed results of this study will be presented in 2 subsequent manuscripts.

### Proposed Statistical Methods

We will assess normality and homogeneity of data for all outcome measures in both groups. If possible, we plan to conduct an intention-to-treat analysis. We will compare our primary measure in both groups from pre- to postassessment using an ANCOVA at a significance level of *P*<.05, with the covariate being baseline CWS, if significantly related to change in CWS from pre- to posttraining. As all our secondary outcome measures are exploratory in nature, we will use a repeated measures design for comparing changes from baseline, midterm, final assessment, and at 6-month follow-up, at a significance level of *P*<.05, with post hoc analysis. For our survey data, we will compare changes between the first and last training sessions using Spearman correlation for the yes/no responses question, a Wilcoxon rank-sum test for the rank order question, and chi-square analysis for Likert scale responses. A subsequent manuscript will have detailed description of our data analysis methods and statistical tests.

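### The tests named for the first-versus-last survey comparison do not fit paired change data: Spearman does not test change, and rank-sum and chi-square ignore the pairing on the plain reading

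*Protocol article*

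**What the plan says.** The Survey Data Analysis section states: "Participants in both groups also completed our custom-designed study survey at the end of each training week". There are three item types:

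- whether each of nine skills is one that "you have difficulty with in your daily life (using yes/no responses")
- an ordering of the nine skills, described as "rank in order of importance (1-9")
- questions on training experience, answered "using a Likert scale 1-7"

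The stated aim is change: "We will assess survey data responses for change in responses, ranking of task difficulty, and change in Likert scale scores, respectively".

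The Proposed Statistical Methods section then fixes the comparison, "For our survey data, we will compare changes between the first and last training sessions", and assigns one test to each item type: "Spearman correlation for the yes/no responses question, a Wilcoxon rank-sum test for the rank order question, and chi-square analysis for Likert scale responses". No paired test is named, and the survey sentence mentions no contrast between the HF and HF+C arms. The section leaves fuller detail to a later manuscript.

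**The concern.** First and last answers come from the same people, so a test of change has to work on within-person differences.

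- **Spearman** has independence of the two occasions as its null hypothesis. People who keep their answers produce a strong correlation and a small P value, so stability can be reported as a significant result.
- **Rank-sum** assumes two independent samples.
- **A contingency chi-square** on a seven-point scale also assumes independent samples, and it discards the order of the categories.

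At stake is what the trial reports about perceived difficulty, importance and training experience. A smaller point is that the analysis sentence refers to training sessions, whereas the survey was taken at the end of each week.

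**Working it through.** **Inputs.** From the Results section: 39 randomized, 19 HF and 20 HF+C. Item scales and survey timing are from Survey Data Analysis. The article gives no within-person correlation and no significance level for the survey. A range of correlations is therefore assumed, with two-sided 0.05 as for the other analyses. Using n=39 assumes everyone supplies both surveys. The article states no error rate or power for the survey, so there is no figure to reproduce.

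**Step 1: Spearman in fixed examples, n=39.**

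- Identical first and last answers (20 yes, 19 no): r = 1, P about 0, with no change at all.
- Everyone moves from no to yes: r is undefined, although change is complete.
- 30 yes falls to 10 yes, with the 10 among the original 30: r = (39×10 − 30×10)/√(30×9×10×29) = 90/279.8 = +0.32, P = 0.046. All 20 discordant pairs go one way, so exact McNemar gives P = 2×0.5^20 = 1.9×10⁻⁶.

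**Step 2: Spearman under simulation, n=39.** Latent bivariate normal answers with correlation ρ are cut to give the stated yes proportions. Entries are the share of trials significant.

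| ρ | Spearman, 60% to 60% | Spearman, 60% to 30% |
|---|---|---|
| 0 | 5% | 5% |
| 0.3 | 24% | 20% |
| 0.5 | 54% | 48% |
| 0.8 | 97% | 93% |

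Exact McNemar over the same range gives 2-4% with no change and 68-96% for the real fall. Spearman's two columns are nearly equal because its result follows ρ and barely responds to whether answers changed.

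Correlating the answer with a time indicator instead turns Spearman into an unpaired test. Splitting at the median, its type I error is 0.018 at ρ = 0.5 and 0.002 at ρ = 0.8.

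**Step 3: rank-sum on first versus last.** For a difference of means, the true variance is 2σ²(1−ρ)/n, whereas an unpaired analysis assumes 2σ²/n. At ρ = 0.7 its standard error is too large by about 1/√0.3 = 1.83. Rank-sum behaves similarly: simulated type I error is about 0.1% instead of 5%. Power for a 0.5 SD shift at ρ = 0.7:

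| n | Rank-sum | Signed-rank |
|---|---|---|
| 39 | 61% | 97% |
| 20 | 25% | 77% |

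With a nine-level scale and ρ = 0 the two tests agree (0.55 and 0.54), so the loss comes from ignoring the pairing.

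**Step 4: contingency chi-square (2×7) on a Likert item, n=39.**

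- Type I error: 0.033 (ρ = 0.5) and 0.015 (ρ = 0.8).
- Power for 0.5 SD: 0.23 and 0.16, against 0.79 and 0.99 for signed-rank.
- At ρ = 0 it is already weaker, 0.28 against 0.54, because it ignores order.
- Average expected count: 78/14 = 5.6 overall; 38/14 = 2.7 (HF) and 40/14 = 2.9 (HF+C). Sparseness is a problem only within an arm.

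**The case against.** **Between-arm reading.** The strongest defence is that the plan may mean per-person changes compared between arms. Both arms completed the survey, and the abstract speaks of each group's experiences. Rank-sum on change scores would then be valid (simulated type I error 0.045), and chi-square on change categories would be usable. This stands as an ambiguity. However, the only contrast in the sentence is "we will compare changes between the first and last training sessions", and a first-to-last correlation of yes/no answers would still not measure change.

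**Generic wording.** Chi-square can also describe paired symmetry tests such as McNemar or Bowker. That is true, so the objection to chi-square rests on reading it as the usual contingency test.

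**Deferred detail.** Deferral to a later manuscript excuses missing detail. It does not excuse three tests already named.

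**Stronger inferences that the article does not support.**

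- *All three tests produce false positives.* Only Spearman does. With positive within-person correlation, the other two err conservatively and miss change.
- *The first survey is presented as a pre-training baseline.* The article never calls it one. By Table 2, HF+C was scheduled for nine challenges per week, so the end-of-week-1 survey follows planned exposure to all nine skills. That matters for interpretation, but the session wording is plausibly just loose.
- *The trial's main conclusions are threatened.* No sample size or efficacy claim rests on the survey.

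**Conclusion.** The point holds in limited form. Spearman is the wrong tool for change in yes/no answers, and no reading that the sentence supports rescues it. With no change, it is significant in anything from 5% to 97% of trials at n=39, depending on an unknown correlation. Rank-sum and chi-square are unsuitable on the plain first-versus-last reading, where the cost is lost power.

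The correlations are assumptions. The size of the effect depends on them, but its direction holds for any positive within-person correlation. The n=39 figures pool the arms and ignore dropout. Paired tests within arms of 19 and 20 have less power: exact McNemar for 60% to 30% with independent answers falls from 68% to about 34% at n=20.

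Severity is moderate to low, because the survey is neither the primary outcome nor among the listed secondary measures.

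**What to change.** Rewrite the survey sentence in Proposed Statistical Methods:

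- Compare the end-of-week-1 survey with the last weekly survey, and drop the reference to first and last training sessions.
- Use exact McNemar for each yes/no item.
- Use Wilcoxon signed-rank for each skill's rank and for each Likert item.
- State whether these comparisons are within arm or pooled. If a contrast between HF and HF+C is intended, say so and apply rank-sum to individual change scores.

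The cost is one sentence. The data are already collected and need no addition.

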## Discussion

Locomotor disability post stroke continues to impede stroke survivors from engaging in active community participation and negatively impacts their quality of life. Given the prioritization of improvement in walking function by stroke survivors and the 2014 AHA exercise training recommendation report, it is all the more vital that poststroke gait interventions incorporate task-specific essential challenging mobility skills, akin to real-world scenarios, along with training at higher cardiovascular intensities to improve functional gains [59]. Through our study, we explored 2 unique gait interventions, ie, HF walking and HF+C walking, using a novel and safe gait training environment to investigate functional ambulation capacity after 6 weeks of training. Our study results will yield important insight on whether individuals post stroke can train at higher intensities, especially while walking without any external handrail support or passive manual assistance at their preferred self-selected BWS level (HF walking) or when practicing essential challenging mobility skills with HF walking (HF+C walking). Although our primary outcome measure is change over-ground CWS, we have also collected various secondary exploratory measures and survey data for both training paradigms. As our secondary measures are most commonly used in clinical settings to assess functional ambulatory capacity, we hope these variables will inform future poststroke studies that plan to use similar gait training paradigms. Our main study outcomes and week-by-week training analysis are being presented in 2 separate manuscripts, respectively. We hope that the results of this study will help in better informing clinicians and researchers on how real-world balance challenges can be incorporated to improve the selection of treadmill training protocols to improve functional walking capacity for individuals post stroke.

## Appendix

Multimedia Appendix 1 Participant Phone Screen Form.

Multimedia Appendix 2 Weekly Community Walking Survey.

## Abbreviations

6MT: 6-min walk test
10MWT: 10-meter walk test
ABC: Activities-Specific Balance Confidence scale
AHA: American Heart Association
ANCOVA: analysis of covariance
BBS: Berg Balance Scale
BWS: Body weight support
COM: center of mass
CWS: comfortable walking speed
DOF: degrees of freedom
FWS: fast walking speed
GDS: Geriatric Depression Scale
HF: hands-free
HF+C: challenge and HF walking
HR: heart rate
KA: KineAssist
KA interface: KineAssist treadmill interface
PI: principal investigator
RPE: rate of perceived exertion
SIS: Stroke Impact Scale
UAB: University of Alabama at Birmingham
